### Recruitment

#### Participants: Patients

An invitation to participate will be posted in several locations at the Glenrose Rehabilitation and Royal Alexandra Hospitals. Hand therapists at both the hospitals will support the recruitment strategies, including the provision of information sessions and one-on-one conversations with potential participants. The first contact with a potential participant will be made through one of the hand therapists not involved in the research team. Therapists who are already involved in the clinical care of the patients will then determine the individuals’ willingness to be approached by the hand therapist researcher regarding participation and obtain their consent for the study.

#### Participants: Therapists

The study coordinator will send out an invitation to participate via email to potential participating therapists, and posters will be put up in the therapists’ staff rooms at the Glenrose Rehabilitation and Royal Alexandra Hospitals.

### Allocation: Sequence Generation

Probability sampling stratified by medical condition (wrist fractures, acquired brain injuries, burns, or osteoarthritis) will be used. Random sequence generation will be prepared in advance by a research team member ([name]) on an Excel file spreadsheet (RAND function) using permuted block randomization with a block size of 4 and a ratio of 1:1.

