### Study Setting

The study will be conducted in 2 health care facilities: the Royal Alexandra Hospital Outpatient Clinic and the Glenrose Rehabilitation Hospital Specialized Rehabilitation Outpatient Program Hand Class. Both institutions are located in Edmonton, Alberta, Canada.

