### Interventions

The eligible participants will be randomly assigned in a 1:1 ratio to either the experimental group or the control group.

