### Allocation: Concealment Mechanism

Allocation concealment will be ensured, as we will not release the randomization code until the patients have been recruited in the trial and all the baseline measurements have been completed.

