### Allocation: Implementation

If a potential participant meets the inclusion criteria, the hand therapist researchers (CH, DY, GD, and JS) will ask the study coordinator ([name]) to check whether a place is available in the study for that participant in a given strata (ie, medical condition). If a place is available, then one of the therapist researchers (CH or DY) or another therapist involved in the recruitment process (JS or GD) will invite the participant to participate in the study, explain the study to him or her, and ask him or her to sign the consent form. If a potential participant is assigned to a particular therapist researcher (CH, DY, JS, or GD), this therapist will not invite this participant to participate in the study. Instead, a secondary therapist researcher will do so. As a result, the freedom to decline will not be compromised. Once the participants or their substitute decision makers have signed the consent form and given their assent, the therapist researchers (CH or DY) will inform the study coordinator ([name]). The study coordinator ([name]) will allocate each participant to one arm of the trial according to the allocation protocol and assign a code. This code will be provided to the therapist researchers (CH or DY) and research assistants (RAs).

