### Blinding (Masking)

The assessments of range of motion and strength measurements and the PRWE questionnaire will be conducted by RAs blinded to the treatment allocation. Due to the nature of the intervention, neither the participants nor the therapist can be blinded to the treatment allocation, but they are strongly encouraged not to disclose the participants’ allocation status during the assessments. An RA will enter the data onto a computer on separate datasheets, and a senior RA will conduct the data analysis under the supervision of the principal investigators ([name] and [name]).

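### A single, published block size of 4 lets unblinded recruiters deduce up to about one third of assignments, so withholding each code until baseline does not secure concealment

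*Protocol article*

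**What the plan says.** The protocol article fixes the following:

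- **Sequence** (Allocation: Sequence Generation): "Probability sampling stratified by medical condition (wrist fractures, acquired brain injuries, burns, or osteoarthritis) will be used". The list is prepared in advance in a spreadsheet with a random-number function, "using permuted block randomization with a block size of 4 and a ratio of 1:1". No variation in block size is stated, and hospital is not a stratum.
- **Sites** (Study Setting): "The study will be conducted in 2 health care facilities", so both hospitals draw on the same sequence within each condition.
- **Concealment** (Allocation: Concealment Mechanism): concealment is claimed because "we will not release the randomization code until the patients have been recruited in the trial" and baseline measurement is complete.
- **Recruiters** (Allocation: Implementation): four therapists may invite and consent patients, after the coordinator confirms that a place is open in the stratum. A therapist to whom a patient is assigned does not invite that patient. The coordinator then allocates and assigns a code: "This code will be provided to the therapist researchers" (two of the four recruiters) and to the research assistants.
- **Blinding** (Blinding (Masking)): "neither the participants nor the therapist can be blinded to the treatment allocation". Outcome assessments "will be conducted by RAs blinded to the treatment allocation".
- **Identifiers** (Confidentiality): participants are given numerical codes in place of names.

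**The concern.** When every block holds two patients per arm, anyone who has seen the earlier assignments in a block can often name the next one, and always the fourth. Treatment starts patient by patient and the device is visible in the clinic, so earlier assignments become known on the treating side as the trial proceeds. Withholding the current patient's code does not remove that knowledge.

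Foreknowledge has room to act. Some exclusions rest on judgement, such as patient-reported limitations and willingness to commit to the program, and the recruiter also conducts the consent conversation. What is at stake is who enters each arm. The primary objective is feasibility, but the between-group estimates and variances are meant to inform a definitive trial, and selection at enrolment would carry into them.

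A smaller matter concerns the assessors. The code assigned at allocation also goes to the research assistants, who are described as blinded, and that section does not say what the code reveals.

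**Working it through.** The article gives no predictability figure, so there is none to reproduce. The inputs are block size 4, ratio 1:1 and 94 patients. The number of patients per stratum is not given, so the splits below are assumed.

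**1. Certain share, complete blocks, fully informed observer.** There are 6 equally likely balanced orders of two A and two B. An assignment is certain once one arm's two slots are used.
- Positions 1 and 2: never certain.
- Position 3: certain if the first two match, 2 of 6 orders = 1/3.
- Position 4: always certain.
- Share = (0 + 0 + 1/3 + 1)/4 = 33.3%.

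**2. Best-guess rate, same observer.** The observer guesses the arm with more slots left and tosses a coin when they are equal. The success rates are 1/2, 2/3, 2/3 (= 1/3 × 1 + 2/3 × 1/2) and 1. The mean is 2.833/4 = 70.8%, against 50% with no information.

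**3. The 94 patients.** A complete block contributes 4/3 certain assignments. A final part-block of two contributes none, and one of three contributes 1/3.

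| Assumed split | Certain assignments | Share |
|---|---|---|
| 94 | 23 × 4/3 = 30.7 | 32.6% |
| 32, 31, 31 | 22 × 4/3 + 2 × 1/3 = 30.0 | 31.9% |
| 70, 10, 10, 4 | 22 × 4/3 = 29.3 | 31.2% |

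That is about 29 to 31 patients.

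**4. Partial visibility.** Let each earlier allocation be seen with probability v (assumed), with the position in the block still known. Certainty requires having seen both earlier assignments to the exhausted arm, which has probability v². Share = (v²/3 + v²)/4 = v²/3.
- v = 1: 33.3%
- v = 0.75: 0.5625/3 = 18.8%
- v = 0.5: 0.25/3 = 8.3%

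**5. Randomly varying blocks of 4 and 6.** This was simulated with the two sizes equally likely and an observer who sees every earlier allocation and knows the possible sizes but not their order. For strata of 24, 31 and 94 patients, the certain share is about 6% in each case and the best-guess rate is about 68–69%.

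**6. Imbalance.** The largest possible difference between arms within a stratum is half a block: 2 with blocks of 4, and 3 when blocks of 6 are included.

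**The case against.** The strongest reply is that no recruiter is shown to have the view that the 33% requires. Two hospitals share each stratum's sequence, the coordinator holds the list, four people share recruitment, staff therapists deliver the sessions, and the codes go to only two of the recruiters, joined by *or*. All of this stands. A reader might infer that one third of assignments will be known to recruiters in general. The documents do not support that, and the one-third figure is a ceiling. They do not remove the risk either: the two recruiters who receive codes come closest to a full view and could pool what they know.

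It could also be argued that the code is withheld until recruitment as a whole has ended. That cannot describe an unblinded device trial in which each patient starts treatment after allocation. The safeguard can only act on one patient at a time.

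A reader might further infer that sending the code to the research assistants undoes assessor blinding. The text does not show this. Allocating to an arm and assigning a code are written as two acts, the Confidentiality section uses numerical codes as participant identifiers, and the Blinding section says that the assistants are blinded. What remains is an ambiguous word.

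Finally, effectiveness is a secondary objective and the analysis stresses description and confidence intervals. That lowers the stakes, but it does not make the concealment claim correct.

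**Conclusion.** The concern holds in a limited form. One small, constant, published block size, combined with unblinded recruiters of whom two receive codes, means that the stated safeguard does not secure concealment against prediction from earlier allocations. Up to about one third of assignments (31–33% of 94 patients) could be deduced before consent. That assumes knowledge of the block size, the position in the block and every earlier allocation in the stratum. At 75% or 50% visibility, which are illustrative values, the share is about 19% or 8%. The documents do not say how much any one recruiter sees, so the true figure within this range cannot be fixed. The assessor point is a request for clarification only.

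**What to change.** - **Block sizes.** For all allocations not yet made, generate the list with randomly varying block sizes, for example 4 and 6. Keep the sizes undisclosed to recruiters and out of any document they use, and freeze the spreadsheet values so that the random-number function cannot recalculate them. The study was launched before it went on hold, so record how many patients, if any, were allocated under the present list.
- **Concealment text.** State that concealment rests on undisclosed, varying block sizes as well as on withholding each code until baseline is complete.
- **Code.** State that the code given to the research assistants is the participant identifier described under Confidentiality and carries no arm information.

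The cost is a new list for the remaining allocations, a few edited sentences, and a maximum within-stratum imbalance of 3 instead of 2. The gain should not be oversold. If the possible sizes become known, certainty falls from about 33% to about 6%, but the best-guess rate falls only from about 71% to 68–69%. Keeping the sizes undisclosed is therefore part of the fix.

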### Allocation: Concealment Mechanism

Allocation concealment will be ensured, as we will not release the randomization code until the patients have been recruited in the trial and all the baseline measurements have been completed.

### Allocation: Implementation

If a potential participant meets the inclusion criteria, the hand therapist researchers (CH, DY, GD, and JS) will ask the study coordinator ([name]) to check whether a place is available in the study for that participant in a given strata (ie, medical condition). If a place is available, then one of the therapist researchers (CH or DY) or another therapist involved in the recruitment process (JS or GD) will invite the participant to participate in the study, explain the study to him or her, and ask him or her to sign the consent form. If a potential participant is assigned to a particular therapist researcher (CH, DY, JS, or GD), this therapist will not invite this participant to participate in the study. Instead, a secondary therapist researcher will do so. As a result, the freedom to decline will not be compromised. Once the participants or their substitute decision makers have signed the consent form and given their assent, the therapist researchers (CH or DY) will inform the study coordinator ([name]). The study coordinator ([name]) will allocate each participant to one arm of the trial according to the allocation protocol and assign a code. This code will be provided to the therapist researchers (CH or DY) and research assistants (RAs).

### Blinding (Masking)

The assessments of range of motion and strength measurements and the PRWE questionnaire will be conducted by RAs blinded to the treatment allocation. Due to the nature of the intervention, neither the participants nor the therapist can be blinded to the treatment allocation, but they are strongly encouraged not to disclose the participants’ allocation status during the assessments. An RA will enter the data onto a computer on separate datasheets, and a senior RA will conduct the data analysis under the supervision of the principal investigators ([name] and [name]).

### Data Collection Methods

#### Primary Objective and Secondary Objectives 1 to 4: Primary Outcome Variables

The AROM and PROM of the wrist extension or flexion, radial and ulnar deviation, and pronation and supination will be measured using a goniometer (Baseline 360-degree, 12-inch clear plastic goniometer); the grip strength will be measured using a dynamometer (Baseline Lite hydraulic, 200 lb); and the pinch strength will be measured using a pinch gauge or pinch meter (Jamar pinch gauges).

#### Primary Objective and Secondary Objectives 1 to 4: Secondary Outcome Variables

The patients’ perceived wrist pain and disability in activities of daily living will be measured using the PRWE [25]. The PRWE is a 15-item questionnaire that assesses 3 components: pain, function during specific activities of daily living, and function during usual activities (personal care, household work, work, and recreational activities). Studies have found this questionnaire to be a valid and reliable assessment tool for evaluating patient-based pain and disability levels in routine clinical practice [26].

All hand therapy sessions for both groups will be conducted in the hand therapy area at the Glenrose Rehabilitation and Royal Alexandra Hospitals by the staff hand therapists. The length and frequency of the sessions for the participants in both groups will be recorded by the therapists. The RAs will measure the AROM, PROM, grip strength, and pinch strength. They will also administer the PRWE to all the participants before (week 0) and after the intervention (week 10) and during weeks 2, 4, and 8. The total time taken to administer the measures will be approximately 60 minutes. The RAs will be trained in the administration of the outcome measurements and adequate use of the assessment tools (eg, dynamometer, goniometer, and pinch meter) by experienced hand therapists.

#### Secondary Objective 5: Estimating the Costs and Resource Use

To estimate the resource use and costs, we will use a single study–based economic evaluation approach (patient-level data). The costs will include resources related to the following categories: (1) the time human resources spend on the sessions will be monitored during the study, whereas the information on the average salaries of the human resources will be taken from the records at each hospital; (2) the capital cost of the equipment used in each intervention and depreciation of the equipment will be calculated using the straight-line depreciation approach; (3) therapeutic supplies (eg, weights and elastic or squeezing supplies); (4) consumables (eg, bandages and sanitization wipes); (5) cost of sterilization, if needed; (6) allowance costs (if any); and (7) maintenance costs (eg, calibration, preventive, and corrective maintenance of equipment). The information on the costs will be taken from the financial records at each hospital. In addition, we will conduct face-to-face interviews with the financial departments at both hospitals to identify the cost components and costing method.

#### Secondary Objective 6: Usability and Technology Acceptance

Once the data collection for the primary objective is completed, semistructured interviews (topic guided) will be conducted with the hand therapists who have agreed to participate and signed a consent form. The interviews with the therapists who used the FEPSim device during their interventions will be audiotaped for later analysis by the team members. The interviews will be conducted by one RA. To ensure anonymity, the therapists’ responses will not be connected to their identities.

### Data Analyses

#### Primary Objective and Secondary Objectives 1 to 4

Data analyses will be conducted using the intention-to-treat principle. Complete case analysis will be the primary method for dealing with missing data equal to or more than 10%. This is the most common method for dealing with missing data and reducing the risk of bias [27]. For missing data of less than 10%, we will use a simple imputation method by replacing the missing data with the average participants in the same strata (ie, medical condition). The analyses will focus on descriptive statistics and CI estimation rather than formal hypothesis testing [28]. Descriptive statistics will be used to characterize the groups at the pretest and posttest as well as during weeks 2, 4, and 8. The outcome variables as well as other data such as the length and dosage of each intervention will be summarized as n (%), mean (SD), or median (IQR), as appropriate. The retention rates, intervention compliance, and missing data will be summarized for outcomes related to the secondary objectives, which, together with the estimates, will assist in calculating the sample size for a definitive trial. As this study aims to assess the feasibility of conducting a definitive trial, clinical effectiveness is a secondary objective (ie, the study’s proof-of-concept element). In this regard, comparisons of the outcome variables at the pretest (week 0) and posttest (week 10) within the groups will be performed using a paired two-tailed *t* test (or a Wilcoxon signed-rank test if the data are not normally distributed) for AROM, PROM, grip strength, and pinch grip force and a Wilcoxon signed-rank test for the PRWE. Comparisons between the groups at the pretest and posttest will be performed using a *t* test (or a Mann-Whitney *U* test if the data are not normally distributed) for AROM, PROM, and grip strength and a Mann-Whitney *U* test for the PRWE. With our sample size, there would be a power of 0.8 to detect a medium effect size of Cohen *d*=0.25. However, we are aware that our study might be underpowered due to the sample size. If no statistically significant differences are found, our results will be classified as inconclusive rather than negative. We will report 95% CIs and interpret the level of uncertainty based on them [28]. In addition, we will explore the effects of the covariates using general linear models or multilevel mixed models when appropriate. All the α levels of significance will be set at *P*≤.05 (two-tailed).

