### Sample Size

#### Primary Objective and Secondary Objectives 1 to 4

As this is a feasibility study, a sample size calculation is not required [17]. However, we can estimate the number of participants we will be able to recruit during the data collection period. According to the clinical partners at the 2 hospitals involved in this study, approximately 167 patients who potentially meet the inclusion criteria will be admitted (accessible population). We aim to recruit 47 participants for each group, for a total sample size of 94 participants, to compensate for a 30% dropout rate. Thus, the recruitment of 94 participants represents 56.3 % (94/167) of the participation rate. This number is based on our ability to detect a small effect size (Cohen *d*=0.25) with 80% power and an α of .05 (two-sided). The sample size calculations were estimated using G*Power software version 3.1.9.4 (Universitat Kiel) [23].

#### Secondary Objective 6

Ten hand therapists from the hand therapy services who have used the FEPSim device will be recruited. Individual interviews will be conducted until either redundancy or theoretical saturation of the data has been achieved [24].

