
#### Secondary Objective 5: Estimating the Costs and Resource Use

For each intervention, descriptive statistics will be used to characterize the categories of the estimated costs (ie, mean [SD] or median [IQR] as appropriate). In this study, missing data costs will be replaced by means or medians, as appropriate. We will quantify uncertainties by reporting the differences between the means and 95% CIs for the categories of the comparator groups’ estimated costs and then interpret the levels of uncertainty based on these [28] and by conducting statistical tests (ie, a *t* test or Mann-Whitney *U,* test as appropriate), while looking for differences in each category of estimated costs between the comparator groups. All α levels of significance will be set at *P*≤.05 (two-tailed).

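### The 10% missing-data rule and the withdrawal rule do not fit the declared intention-to-treat analysis, and the effect and variance estimates can be distorted when dropout differs by arm or gaps are filled with one mean

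*Protocol article*

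**What the plan says.** The Data Analyses section for the primary objective and secondary objectives 1 to 4 fixes the rule itself, so it is not a detail left to another document.

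- Principle: "Data analyses will be conducted using the intention-to-treat principle".
- At or above the threshold: "Complete case analysis will be the primary method for dealing with missing data equal to or more than 10" percent. Reason given: "This is the most common method for dealing with missing data and reducing the risk of bias".
- Below the threshold: simple imputation by "replacing the missing data with the average participants in the same strata (ie, medical condition"). Arm is not mentioned. Nor is it said whether the 10% is counted per variable, per visit or overall.
- Comparisons between arms are t tests or Mann-Whitney tests at weeks 0 and 10. Weeks 2, 4 and 8 are described. Multilevel mixed models are named only for exploring covariates.

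The Sample Size section reads "We aim to recruit 47 participants for each group, for a total sample size of 94 participants, to compensate for a 30% dropout rate". The section Withdrawal From the Study says that a withdrawn participant's information is left out of the analysis, and treats destruction of data as a separate request. Under secondary objectives 3 and 4 and in Data Analyses, the estimates, variances and 95% confidence intervals are to inform the definitive trial's sample size.

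**The concern.** Three things do not fit together. An intention-to-treat comparison that leaves out about 30% of those randomised, and deletes withdrawn participants altogether, no longer compares the groups as randomised. The reason given for complete-case analysis is wrong: at best it adds no bias, and it never removes any. The low-missingness branch replaces a participant's value with a mean shared by both arms, which pulls the arms together and understates the spread.

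At stake are the between-group estimate and its variance, which the plan wants to carry into the definitive trial. A relation between dropout and response that differs by arm is possible here. The Blinding section says that neither participants nor therapists can be blinded, and the Discussion hopes that the device will speed recovery and shorten treatment.

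**Working it through.** **Which branch applies at week 10.** Expected loss is 0.30 × 94 = 28.2, leaving 65.8, about 33 per arm. Since 30% exceeds 10%, the complete-case branch is the one implied.

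**Complete-case branch.** From the plan: 47 per arm, 30% dropout, and 0.25 as the size of a standardised difference. Assumed: SD 1; dropout driven by the week-4 score Z (measured from its arm mean) with log-odds b = 1 per SD; correlation r = 0.5 to 0.7 between weeks 4 and 10.

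In an affected arm, the mean week-10 value of those who stay moves by r × E[Z | stays], where P(stays | Z) = 1 − expit(a + bZ) and a is set to give 30% dropout. Numerical integration gives |E[Z | stays]| = 0.253, so the shift per affected arm is 0.5 × 0.253 = 0.126 to 0.7 × 0.253 = 0.177.

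| Dropout relation | Complete-case average (truth 0.25) |
|---|---|
| Random | 0.25 |
| Same in both arms | 0.25 (0.23 to 0.24 if the raw score drives dropout, because the arms already differ at week 4) |
| One arm only, r = 0.5 | 0.25 ± 0.126 = 0.12 or 0.38 |
| One arm only, r = 0.7 | 0.25 ± 0.177 = 0.07 or 0.43 |
| Opposite in the two arms, r = 0.5 | 0.25 ± 0.253 = 0.00 or 0.50 |
| Opposite in the two arms, r = 0.7 | 0.25 ± 0.354 = -0.10 or 0.60 |

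The outer limits move by a few hundredths with the way dropout is set: a simulation with about 33% dropout in affected arms gave -0.14 and 0.64. In that simulation (8,000 replicates), an estimate using the week-4 score of everyone randomised averaged 0.25 in every scenario.

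A weaker relation does much less. With b = 0.3 and r = 0.5, E[Z | stays] is 0.088 in size and the shift is 0.5 × 0.088 = 0.04 SD. The standard error at 33 per arm is √(2/33) = 0.25 SD.

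**Branch below 10%.** Take 4 of 47 missing per arm (8.5%), completely at random, with strata that explain no variance.

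- *Mean pooled over arms (the literal reading).* The difference is multiplied by about 1 − 4/47 = 0.915, so 0.25 becomes 0.229. The variance is multiplied by about 42/46 = 0.913 (0.918 simulated). At 9% missing with strata, another simulation gave an SD of 0.965, a variance of 0.965² = 0.93. Required sample size is proportional to variance, so it comes out about 7 to 9% too small.
- *Mean within arm.* The difference is unbiased. The reported standard error is 0.197 against a true √(2/43) = 0.216, a ratio of 0.91. Coverage of the 95% interval is 2Φ(1.96 × 0.91) − 1 ≈ 0.93; simulations gave 92.6 to 93.1%.

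**The case against.** The strongest case for leaving the rule alone is that this is a feasibility trial. Its primary objective rests on retention and compliance, which the rule does not touch. Effectiveness is a secondary, proof-of-concept aim; intervals come before tests; missing data will be summarised; and non-significant results will be called inconclusive. The sampling error of about 0.25 SD is larger than the one-arm shifts above. All of this stands, and it lowers the severity. It does not make the rule sound, because the estimates and variances are named products of the trial.

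Four stronger readings are tempting, and the documents do not support them:

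- *Complete-case analysis is biased whenever dropout relates to early response.* The relation must differ between arms. No passage says that it will, or in which direction.
- *Error is understated at 30% dropout.* That fault belongs to mean filling, which applies only below 10%. It could govern earlier visits or single variables, but not week 10 at the planned dropout.
- *The week 2, 4 and 8 data are thrown away.* They are still described. They go unused in the week-10 contrast because the chosen tests compare single time points, and the plan nowhere says that complete case means deletion across all visits.
- *The complete-case branch is certain.* The 30% is a recruitment allowance, and retention is itself an outcome to be estimated.

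**Conclusion.** The concern holds in this limited form. The text contradicts itself: intention-to-treat is declared, while complete-case analysis at 10% or more and the exclusion of withdrawn participants are prescribed. The reducing-bias justification is wrong.

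Bias at week 10 is conditional. It is about zero if dropout is random or acts alike in both arms. For a true 0.25 SD, complete-case analysis averages about 0.07 to 0.43 if one arm is affected and about -0.1 to 0.6 if the arms run in opposite directions. These figures rest on the assumed log-odds of 1 per SD and correlation of 0.5 to 0.7. The actual size and direction cannot be known from the documents.

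The low-missingness fault is smaller but does not need outcome-related dropout: about 9% shrinkage of the difference with a variance 7 to 9% too small, or about 93% coverage if the mean is taken within arm. This should be fixed, but it does not undermine the feasibility aim.

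**What to change.** In Data Analyses:

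1. Delete the 10% switch, the single-mean imputation and the statement that complete-case analysis reduces bias.
2. Make the multilevel mixed model already named there the main week-10 between-group estimate for range of motion, grip strength and pinch strength. Fit it to all observed visits of all randomised participants, with arm, visit, arm-by-visit, medical condition and baseline. Report the week-10 difference with its 95% interval.
3. Use the same model for the PRWE total score, with the rank test as a supporting analysis.
4. Keep complete-case analysis as a sensitivity analysis, and state the missing-at-random assumption.

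In Withdrawal From the Study: keep data collected before withdrawal unless the participant asks for their destruction. Without this change the model cannot use everyone randomised.

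Cost: no new visits or measurements, since the five time points are already scheduled, and a little more analysis work. The withdrawal change also needs a check that the consent wording matches. The model relies on missing at random. If dropout depends on the unseen week-10 value itself, bias can remain, which is why the assumption must be stated.
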